#### Resident recruitment

Care home managers will be asked to identify eligible residents in their care home. For those clearly not eligible, the following non-identifiable data will be recorded: care home, age, sex, ethnicity, and reason for exclusion.

All eligible residents will be asked by care home staff if they are willing to be seen by researchers so they can explain the study. If they agree, a researcher, accompanied by a member of care home staff will then explain the study to the resident and assess for capacity to consent. If residents have capacity they will be asked for consent to participate in the study. Residents who consent will also be asked about their views on future participation should their capacity fluctuate (through worsening dementia or a delirious episode). For residents without capacity, the advice of a consultee will be sought if there is no advanced directive in place pertaining to participation in research.

A protocol amendment has been put in place in order to undertake further recruitment of residents at 12 months post-intervention (2 to 4 months prior to the outcomes assessments). This will mitigate the effect of attrition in this extremely frail and elderly population and subsequent loss to follow-up. It will also allow us to investigate the feasibility of alternative approaches to the timing of recruitment.

Additional recruitment will take place in all care homes participating in the study. Care will be taken to spread additional recruitment over both the intervention and control arms. Residents will only be considered for recruitment at this stage if they have moved into the home subsequent to the first round of recruitment (those who have already been approached and refused will not be approached again). All other eligibility criteria will apply.

Additional residents will be recruited during the intervention and will provide baseline and follow-up assessment data in the same way as those recruited earlier.

We are conscious that a two-tier recruitment strategy may lead to differential recruitment, as randomisation to the intervention or control arm has already taken place; however, additional recruitment will not be used as a covariate in analyses.

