### Analysis

In this pilot trial, quantitative analysis will focus on descriptive statistics and will focus on confidence interval estimation rather than formal hypothesis testing. An intention-to-treat-analysis of clinical data will be undertaken blind to allocation. Any statistical analysis in a definitive trial would include multilevel modelling to account for the cluster design. Qualitative data from interviews and focus groups will be analysed combining a grounded theory (constant comparison) approach and narrative analysis to develop understanding of the factors (such as contextual, leadership, and organisational structures and knowledge, beliefs and behaviours of staff) that facilitate or inhibit sustainability of the intervention and its integration into routine practice over time.

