#### Outcome assessments

The delirium occurrence rate for intervention and for control arms will be calculated (number of residents with an episode of delirium in one month/total number of residents screened). A 95% confidence interval for the difference in rates will be constructed. Intraclass coefficients will be calculated for delirium occurrence using data from the post-intervention period. Summary statistics and comparisons between the intervention and control arms post-intervention will also be calculated for all primary and secondary outcomes as detailed previously. Recruitment and attrition will be summarised, together with rates of consent, consultee consent, withdrawals and deaths. In addition, Kaplan-Meier survival curves will be constructed for the following outcomes:

1. Time to first hospital admission in previous 6 months.

2. Mortality in previous 6 months.

Outcomes for hospital admission and mortality are assessed starting 10 months after randomisation. This is because we hypothesise that the intervention will not be able to influence outcomes before that time as it provides education for staff, which they need to operationalise into actions that will then affect residents. We have not therefore collected data for events occurring between randomisation and 10 months for hospital admission. We will have information on deaths and will present a summary of these data for the intervention and the control homes.

Data from the first and second stages of resident recruitment will be analysed together with a separate sensitivity analysis to investigate the impact of the later phase.

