## Discussion

We have made the following modifications to the original planned protocol: i) increased the number of homes to be included from 12 to 14; ii) included residential as well as nursing homes; iii) introduced additional recruitment of residents at 12 months post-randomisation of homes (2 to 4 months before the post-intervention outcomes assessments); and iv) replaced the SCRQoL with the DEMQOL at post-intervention data collection. These changes will help us investigate the feasibility of alternative approaches to recruitment and quality of life assessments. Modifications have been agreed on by the study sponsor and funder, and have received Ethics Committee approval.

Although yet to be confirmed by the results of this pilot trial, we anticipate that the definitive trial will have a shorter intervention period (between 10 to 16 months), that recruitment of residents will take place nearer to the outcome assessments, and that an alternative method of delirium screening will be used.

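### The Kaplan-Meier curve planned for time to first hospital admission, built in the usual way, overstates the probability of admission because death is a competing event

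*Protocol article*

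**What the plan says.** Under Analysis, Outcome assessments, the protocol article states that "Kaplan-Meier survival curves will be constructed for the following outcomes". It lists two: "Time to first hospital admission in previous 6 months" and "Mortality in previous 6 months". Death is not part of the admission event; it has its own curve over the same window. The section places that window in time: "Outcomes for hospital admission and mortality are assessed starting 10 months after randomisation". With outcome collection at 16 months, it runs from month 10 to month 16.

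On deaths, the same section adds: "We will have information on deaths and will present a summary of these data for the intervention and the control homes". Resident recruitment explains the second recruitment round: "This will mitigate the effect of attrition in this extremely frail and elderly population and subsequent loss to follow-up". No death rate, attrition rate or admission rate is given anywhere. The Analysis section says that the quantitative work "will focus on confidence interval estimation rather than formal hypothesis testing". The article does not state how a death before any admission enters the admission curve.

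**The concern.** Death removes a resident from any further chance of admission. A Kaplan-Meier curve that censors deaths treats those residents as if they could still be admitted later at the same rate as the survivors. One minus that curve then describes admission in a setting without death, not the share of residents who are actually admitted.

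Fewer hospital admissions is the secondary hypothesis for the main trial (Aims and objectives). Table 1 asks for admission rates in intervention and control homes and includes time to first admission among the outcomes. The pilot also puts estimation ahead of testing, so a display that overstates the quantity of interest matters even without a p-value. If mortality differs between arms, the overstatement differs too, and the visual comparison of the admission curves is affected.

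**Working it through.** The plan gives no figure to reproduce on this point. The check covers direction first, then size on assumed rates.

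**Direction.** At each admission time, let *d* be the number of first admissions and *Y* the number still alive and unadmitted.

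- One minus Kaplan-Meier, with deaths censored, adds (Kaplan-Meier survival from admission just before that time) × *d*/*Y*.
- The cumulative incidence adds (probability of being both alive and unadmitted just before that time) × *d*/*Y*.

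The second multiplier is never larger than the first and is smaller after any death. So one minus Kaplan-Meier is never below the cumulative incidence, and it exceeds it once an admission follows a death. This needs no assumption about rates.

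**Size.** Inputs, all assumed because the documents give none: constant hazards over the 6-month window; *a* = one-minus-Kaplan-Meier admission risk at 6 months; *d* = 6-month death risk in the absence of admission.

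- Cumulative hazards: La = −ln(1 − a) and Ld = −ln(1 − d).
- One minus Kaplan-Meier, deaths censored: 1 − exp(−La) = a.
- Cumulative incidence: La/(La + Ld) × [1 − exp(−(La + Ld))].

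Worked case, a = 30% and d = 15%: La = 0.3567 and Ld = 0.1625, sum 0.5192. The cumulative incidence is (0.3567/0.5192) × (1 − 0.70 × 0.85) = 0.687 × 0.405 = 27.8%. The overstatement is 30.0 − 27.8 = 2.2 points.

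| Assumed 6-month death | Cumulative incidence when 1 − KM = 30% | Overstatement (points) | Relative |
|---|---|---|---|
| 0% | 30.0% | 0 | 0% |
| 5% | 29.3% | 0.7 | 2% |
| 10% | 28.6% | 1.4 | 5% |
| 15% | 27.8% | 2.2 | 8% |
| 20% | 27.1% | 2.9 | 11% |
| 30% | 25.5% | 4.5 | 18% |

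Over the wider grid, the smallest overstatement is 0.25 points (death 5%, admission 10%) and the largest is 5.85 points (death 30%, admission 40%). In relative terms the range is about 2% to 19%, and it depends on the death rate far more than on the admission rate.

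**Between arms.** Suppose both arms have the same admission hazard (a = 30%), with death of 10% in one and 20% in the other. The two censored curves coincide at 30%. The actual admission probabilities are 28.56% and 27.07%, a difference of 1.49 points that the curves do not show.

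**The case against.** The strongest reply is that the article names a curve but no censoring rule. Deaths could be counted in a composite event, or residents who died could be kept at risk to the end of the window, which gives the cumulative incidence when there is no other censoring. An analysis plan that is not shown might say so. That stands against any claim that the protocol commits to censoring deaths. It does not remove the point: neither alternative is the ordinary meaning of the named method, and either would have to be stated. Keeping the dead at risk also relies on complete follow-up across the window, yet the protocol "introduced additional recruitment of residents at 12 months post-randomisation of homes", which is after the window opens at month 10.

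Second, a death-censored curve is a legitimate display of the cause-specific admission hazard. That is true, but it is then not a display of how many residents are admitted, and a reader will naturally take it as one.

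Third, a reader might infer that the document shows heavy mortality. It does not: the support is qualitative, and attrition also covers losses other than death.

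Fourth, a reader might infer that the definitive trial would be sized on this curve. The Sample size section instead uses a 14% control rate of delirium and a one-third reduction, and the intraclass coefficient is sought for delirium occurrence. Data quality treats time to admission as one of three hospital measures to be compared for completeness.

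Finally, the curve supplements summary statistics that include the number of admissions, and sampling error is likely to be larger than the bias. As an assumed illustration, 100 residents per arm with 30% admitted gives a 95% half-width of 1.96 × √(0.3 × 0.7/100) ≈ 9 points before clustering. This limits the weight of the point, not its direction.

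**Conclusion.** The point holds in a limited form. The protocol names Kaplan-Meier for a non-fatal event that death precludes, in a population it describes as very frail, and it records death over the same window. On the ordinary construction the curve overstates the actual probability of admission, and unequally between arms if mortality differs. The direction is certain once deaths are censored. The size is not known: about 0.25 to 6 percentage points on the assumed ranges and constant hazards, and zero if nobody dies. What is affected is a descriptive secondary display in a pilot; the primary delirium outcome and the basis of the sample size are untouched. The documents do not support saying that deaths must be censored under this plan, that mortality is known to be high, or that the main trial's size rests on this curve.

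**What to change.** In Outcome assessments, replace the Kaplan-Meier curve for first hospital admission by a cumulative incidence (Aalen-Johansen) curve by arm, with death before admission as a competing event. Show it beside the mortality curve, for which Kaplan-Meier remains suitable.

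The planned mortality curve already needs times of death, so no new data are required. The cost is a sentence of analysis wording and minor analysis work.

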#### Resident data

Screening and baseline data for residents will be collected before randomisation. Post-intervention outcome data will be collected at 16 months post-randomisation.

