### Post-intervention assessments

Researchers, blind to allocation, will collect data 16 months from randomisation - deemed to be the start of the intervention - through administering tests on alternate days (except Sundays) for a period of one month and examining individual care home and hospital records. Researchers will record;

1. Presence of delirium on any day during a 1-month post-intervention period. Screening will use the 6-CIT and short version CAM. Presence or absence of delirium for those positive will be confirmed using the DRS-R-98 (as at study baseline). Ratings for a 10% subsample will be compared to determine inter-rater reliability.

2. Delirium severity (proportion of residents with DRS-R-98 severity scale score >15.25 at any assessment) during the 1-month post-intervention period.

3. Delirium duration (days positive for delirium) during the 1-month post-intervention period.

4. Number of medications.

5. Activity of Daily Living (ADL) scores.

6. Falls during previous 6 months.

7. Mortality during previous 6 months.

8. Hospital admissions during previous 6 month including;

a. total length of stay

b. number of admissions

c. time to first admission

The 6-CIT is a dementia screening tool used in primary care. The short CAM is a four-question instrument used extensively for delirium screening and diagnosis [26]. The DRS-R-98 is a valid measure of delirium occurrence and severity [27]. We know that the training of the researcher affects performance of these instruments [34]. Researchers will be trained before both the baseline and post-intervention assessments. As part of the analysis, we will also check inter-rater reliability at baseline by comparing ratings for a 10% subsample.

If a resident scores positive on the short CAM, indicating a possible delirium, subject to prior consent, the care home manager will be informed in writing on the day of assessment so that appropriate action can be taken. A copy of this letter will be held on file with the consent forms.

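### The fixed month 10 to 16 look-back gives residents recruited from month 12 two to four months in which they could not die, so pooled 6-month mortality is biased downwards

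*Protocol article*

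**What the plan says.** Resident data in the protocol article sets the outcome time: "Post-intervention outcome data will be collected at 16 months post-randomisation". Post-intervention assessments lists falls, hospital admissions and deaths over the preceding half-year, for example "Mortality during previous 6 months". Outcome assessments in the Analysis section gives the start of the window, "Outcomes for hospital admission and mortality are assessed starting 10 months after randomisation", and plans Kaplan-Meier curves for "Time to first hospital admission in previous 6 months" and "Mortality in previous 6 months".

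The Discussion reports that the protocol "introduced additional recruitment of residents at 12 months post-randomisation of homes (2 to 4 months before the post-intervention outcomes assessments"). Resident recruitment limits who can join then: "Residents will only be considered for recruitment at this stage if they have moved into the home subsequent to the first round of recruitment". The same section says that these residents supply baseline and follow-up data just as earlier recruits do, that the extra recruitment takes place in every home and will be spread over both arms, that differential recruitment is possible because allocation has already happened, and that recruitment stage will not be a covariate. On the analysis, Outcome assessments says: "Data from the first and second stages of resident recruitment will be analysed together with a separate sensitivity analysis" of the later phase.

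**The concern.** One calendar window, opening at month 10, is applied to people who enter the study two to four months after it opens. A resident who died between month 10 and the second recruitment round cannot be a second-stage recruit. If late recruits are counted over the whole window, they add to the denominator for months in which no death among them could be recorded. Mortality in the pooled sample is then understated, and the early part of the survival curve is too flat.

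Admissions and falls raise a narrower problem. A late recruit who moved in after month 10 has window time before living in the home. Events in that time reflect care given elsewhere.

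The stake is in the planning figures. Table 1 names hospital admission rates by arm as a study question, and fewer admissions is the main trial's secondary hypothesis. The Discussion also expects the definitive trial to recruit residents nearer to the outcome assessment, so the same window would affect more residents there.

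**Working it through.** **1. The window.** Outcome collection at month 16 (Resident data) less a six-month look-back (Post-intervention assessments) gives 16 − 6 = 10 months, which matches the start stated in Outcome assessments.

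**2. Immortal time per late recruit.** Late recruits enter 2 to 4 months before assessment (Resident recruitment; Discussion). Window time before entry is 6 − 4 = 2 months to 6 − 2 = 4 months, or 2/6 = 33% to 4/6 = 67% of the window. For death this holds for every late recruit.

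**3. Effect on pooled mortality.** The article gives neither the mortality nor the share of late recruits. Assumptions:
- true 6-month mortality q = 10%, 15% or 20%;
- the same constant monthly hazard in both stages, h = −ln(1 − q)/6;
- late recruits' time u from entry to assessment uniform over 2 to 4 months;
- late-recruit share f = 25% or 50%.

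Apparent 6-month risk in late recruits is the mean of 1 − exp(−hu) over u from 2 to 4, that is, 1 − [exp(−2h) − exp(−4h)]/(2h). Pooled risk is (1 − f) × q + f × (late risk). With no censoring before month 16, a Kaplan-Meier estimate that starts everyone at month 10 ends at this same proportion.

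| q | h per month | Late recruits show | Pooled, f = 25% | Pooled, f = 50% |
|---|---|---|---|---|
| 10% | 0.0176 | 5.1% | 8.8% (−12%) | 7.6% (−24%) |
| 15% | 0.0271 | 7.8% | 13.2% (−12%) | 11.4% (−24%) |
| 20% | 0.0372 | 10.5% | 17.6% (−12%) | 15.3% (−24%) |

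Percentages in brackets are relative to q. The relative bias depends mainly on the share of late recruits and hardly on the mortality level.

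**4. Between-arm comparison.** With equal shares and equal hazards, both arms shrink by the same factor and the mortality ratio stays at 1.00. With no true effect but assumed shares of 30% in control and 50% in intervention, at q = 15%:
- control: 0.7 × 0.150 + 0.3 × 0.0779 = 0.1284;
- intervention: 0.5 × 0.150 + 0.5 × 0.0779 = 0.1140;
- ratio: 0.1140/0.1284 = 0.89.

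Across q = 10% to 20% the ratio is 0.886 to 0.890. If the shares are swapped, the bias runs the other way (1/0.89 ≈ 1.12).

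**5. Admissions and falls.** Second-stage eligibility requires only a move-in after the first round. A late recruit who moved in by month 10 spent the whole window in the home (apart from any hospital stay), and earlier events can be read from records. Only those who moved in after month 10 have window time outside the home, and the article does not say how many these will be.

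**The case against.** The strongest reply is that the article nowhere says that time before entry counts as time at risk. It gives a calendar window and announces the curves, but sets no time origin or risk-set rule for second-stage residents; an analysis plan that is not shown could specify delayed entry. This stands as a limit on certainty. Still, the fixed window, the identical follow-up, the pooling and the absence of a stage covariate, followed as written, produce the bias.

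A second reply is the planned sensitivity analysis. If it sets second-stage residents aside, it would show first-stage results free of this problem. That may expose the bias, but it leaves the pooled curves and summaries uncorrected.

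Two stronger readings are tempting. A reader might infer that a spurious intervention effect is likely because late recruitment follows an open allocation. The article does not support this: it concedes that differential recruitment is possible, but it recruits in all homes and intends to spread the additions over both arms. A reader might also infer that admissions before move-in will be missing. The article draws on hospital records, collects the NHS number and hospital ID, and compares home records with centralised data, so admissions can be captured. What remains is that those events precede life in the home.

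Finally, this is a descriptive pilot, and neither the one-month delirium outcome nor its intraclass coefficient uses the look-back. That stands, and it lowers the severity.

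**Conclusion.** The point holds for mortality as the text is written: every second-stage resident carries 2 to 4 months of immortal time in a six-month window, and pooled 6-month mortality is biased downwards. The size, about 12% to 24% in relative terms, rests on assumed values: late-recruit share 25% to 50%, true 6-month mortality 10% to 20%, a constant hazard common to both stages, and uniform entry. The ratio of about 0.89 illustrates what shares of 30% and 50% would do; it does not predict an imbalance. For admissions and falls, the problem of time outside the home is confined to late recruits who moved in after month 10. The damage is to secondary descriptive outcomes and to planning figures for the definitive trial, so this is a moderate issue and does not threaten the pilot's main result.

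**What to change.** State in the analysis section that:

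- in the pooled Kaplan-Meier curves, second-stage residents enter the risk set at their recruitment date (delayed entry);
- their admissions, length of stay and falls are counted from recruitment and reported per resident-month at risk;
- the fixed six-month summaries of mortality, admissions and falls are given for first-stage residents only.

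If the existing analysis plan already does this, a cross-reference is enough.

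The cost is a few sentences, slightly more analysis work and less person-time from late recruits. Each second-stage resident's recruitment date is needed. Counting from recruitment avoids relying on the move-in date, which the article's baseline data list does not include. Data collection otherwise stays as planned.
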